## Introduction

### Context/background

Due to the high prevalence of opioid use and elevated risk of overdose among justice involved adults, jails offer an unmatched opportunity to identify and offer treatment to those with opioid use disorder (OUD). From a public health perspective, jails are critical intervention touchpoints, as these facilities typically admit more than 7 million adults per year in the US, holding individuals for an average of 32 days prior to release [1]. In Massachusetts, individuals released from incarceration have a 120 times higher rate of opioid-related overdose deaths compared to the remainder of the adult population [2]. Some jails have responded to the opioid crisis by expanding access to medication for opioid use disorder (MOUD) [3]. However, the optimal strategies for providing MOUD in jails—such as the most appropriate type and timing of treatment—are not well established.

One clinical consideration is whether XRB should be offered to pre-trial detainees with OUD. Relative to its more commonly used counterpart—daily SLB—XRB offers several potential advantages in jail, including: easier logistics of administration, reduced risk of diversion, reduced experiences of patient stigma due to the less regular dosing schedule, and an increased bridge of protection between the time of discharge and admission to community-based MOUD [4]. In prior analyses in Massachusetts jails, it was found that typical SLB retention rates upon release to the community were 80.6% for those prescribed SLB and 86.7% for those prescribed methadone within 30-days of release [5] (Personal communication), and a number of barriers to community connections and ongoing MOUD treatment continuity could lead to breaks in continued buprenorphine and methadone treatment [6, 7] (Stopka et al., 2024; Matsumoto et al., 2023). Because the release date for pre-trial detainees is variable and uncertain, early induction could ensure that persons released precipitously (e.g., from court without notice) will have a clinically active dose of buprenorphine in their system to protect them against post-release overdose. Early induction onto XRB is also more expensive than SLB.

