### Study sites

The site for participant recruitment, data collection, and treatment will be the MJHOC. Middlesex is the most populous county in Massachusetts and New England [9]. The facility includes a House of Correction, which holds people who are sentenced, and a jail, which holds people awaiting trial. As of June of 2025, 526 pre-trial detainees were being held at MJHOC [[name], 2024, 2 Questions, personal communication]. This study will only include unsentenced, pre-trial detainees (Table 1).

**Table 1 Tab1:** Data sources and measures

Measures	Data source	Screening	Pre-release	Post-release
Screening (adult, SLB, unsentenced, 4 days-6 months anticipated jail stay, willing to be randomized)	Electronic medical record (CorEMR), Offender Management System (OMS), self-report	X		
Baseline	Self-report		X	
* Demographics*				
* OUD history*				
* MOUD history*				
Dosing schedule (SLB and XRB)	CorEMR		X	
Liver function test (LFT)	CorEMR		X	
Urine drug screening	CorEMR		X	
Medication diversion incidents	OMS and Inner Perimeter Security (IPS) unit		X	
Number of days Buprenorphine protection post-release (7 days)	CorEMR, OMS			X
Enrollment in community based MOUD (90 days)	Community clinics			X
* # of appointments*				
* Medication type*				
* Dose amount*				
Recidivism (90 days)	Criminal Justice Information Services (CJIS)			X
* # of arraignments*				
* Types of charges/offenses*				
* # of incarcerations*				
* # of convictions*				
Death (90 days)	Various sources (Massachusetts Office of vital statistics, National death index, Google)			X

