#### Secondary and tertiary outcome measures

The secondary outcome measure is MOUD continuation in the community. This outcome will be based on community clinic records indicating admission and retention at 90-days following release, measured as the number of SLB doses or XRB injections received in the community. Tertiary outcome measures involve a range of incidents including death, diversion, disciplinary actions, as well as recidivism outcomes at 90 days post release. Recidivism will be defined as arraignments, types of charges/offenses, incarcerations, and convictions. Data will be acquired through the jail from Criminal Justice Information Services (CJIS) records.

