We will use a modified intention-to-treat (mITT) approach. The primary analysis sample will be participants randomized and released to the community. Clinical trials in the criminal legal system usually see a small rate of randomized participants initially planning for release, then sentenced, transferred, or otherwise incarcerated for longer periods of time due to unanticipated post-randomization factors independent of the study. This effectively renders the now randomized participant ineligible, as they are unable to leave the jail and continue treatment in the community. Thus, participants not released to the community as planned will be excluded from the analysis of the primary outcome. Participants who are not released to the community do not enter the risk set for outcomes that can only be observed at release or in the community after release. While we do not expect arm differences in the probability of release to the community, we will examine this as an exploratory outcome descriptively and with a Fisher’s exact test in intent-to-treat (ITT) analysis. In other ITT analyses, the approach will be outcome-dependent. For the outcomes of buprenorphine in a participant’s system at release and participation in MOUD treatment following release, these participants would be coded as No. For buprenorphine diversion during incarceration, these cases need no special treatment since the outcome does not depend on release. For rearrests, ITT analysis would code these participants as not rearrested. In all modified intent-to-treat (mITT) or per protocol analysis of outcomes observed at or after release to the community, participants not released to the community will be excluded. We expect this to occur among fewer than 5% of all participants who are randomized. Secondary analyses will examine all randomized participants (ITT) and participants both inducted and released as planned (per protocol). Sensitivity analyses will examine the effect of competing risks (i.e. incarceration or death) after release on the primary outcomes.

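### The 90-day recidivism definition is not limited to offences after release, so in a pre-trial cohort a conviction or incarceration on the index case can be counted as recidivism

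*Protocol article*

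**What the plan says.** Under Secondary and tertiary outcome measures, recidivism is a tertiary outcome ("as well as recidivism outcomes at 90 days post release"). Its content is fixed in one sentence: "Recidivism will be defined as arraignments, types of charges/offenses, incarcerations, and convictions". The source is named next: "Data will be acquired through the jail from Criminal Justice Information Services (CJIS) records". Table 1 repeats the components as separate measures. It lists the number of arraignments, of incarcerations and "of convictions", plus the types of charges, with no split between index and new cases.

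The population is fixed under Study sites: "This study will only include unsentenced, pre-trial detainees". The Context/background section builds its rationale on unpredictable release: "Because the release date for pre-trial detainees is variable and uncertain, early induction could ensure that persons released precipitously" would still be covered by medication, with unannounced release from court as the example.

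Planned analyses deals with participants who are never released. For outcomes seen only at or after release, "Participants who are not released to the community do not enter the risk set", and they are left out of the mITT and per-protocol analyses. In the ITT analysis, which is secondary, they receive a value: "For rearrests, ITT analysis would code these participants as not rearrested". The article expects fewer than 5% of those randomized to be in this position.

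**The concern.** A recidivism measure is meant to capture new offending. In a sentenced cohort the index case has already been decided, so a conviction after release points to something new. Here the index case may still be open when the participant leaves. The court can then convict or incarcerate the person on the original charge during the 90-day window, and the event appears in CJIS as a conviction or an incarceration. Applied literally, the definition counts it.

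Two things are at stake. The absolute recidivism rates in both arms would be too high for what the label claims. Events that have nothing to do with treatment would also be added to both arms, which pulls the ratio between arms towards 1. Recidivism is one of the four comparisons named in the abstract and in the design overview, so the result will be read even though the outcome is tertiary.

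**Working it through.** **Plan's own figure.** No rate or power is stated for recidivism. The only power statement concerns the primary outcome: risk ratio 1.34, 75% with XRB, power 0.80. It implies 75/1.34 = 55.97% with SLB. With two-sided alpha 0.05 (assumed), that needs 97 per arm, and 100 per arm gives power 0.813. The figure reproduces, and the present point does not depend on it.

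**Reading the definition against the population.**

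1. Eligible people are all unsentenced, so at randomization every index case is undecided.
2. Some are released while still pre-trial. The article's rationale rests on this.
3. For these people, a later conviction or incarceration on the index case is a CJIS event within 90 days of release.
4. The definition lists convictions and incarcerations without an offence date or case restriction, so the event qualifies.
5. The same court decision is handled differently by timing. If it comes before release and keeps the person in custody, the person is excluded (mITT) or scored as not rearrested (ITT). If it comes after release, it can count as recidivism.

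**Illustration of size.** All rates here are assumptions. Take one component, such as at least one incarceration within 90 days. Let p be the new-offence rate, and q the chance of an index-case event, equal in both arms and independent of new offending. Then the observed rate is 1 − (1 − p)(1 − q).

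With p = 30% and 15%, and 95 per arm (100 less 5% not released):

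| q | Observed rates | Risk ratio | Power | Index-only share of events, higher-rate arm |
|---|---|---|---|---|
| 0 | 30.0% vs 15.0% | 0.50 | 0.70 | 0% |
| 10% | 37.0% vs 23.5% | 0.64 | 0.53 | 19% |
| 20% | 44.0% vs 32.0% | 0.73 | 0.40 | 32% |
| 30% | 51.0% vs 40.5% | 0.79 | 0.31 | 41% |

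Example for q = 20%: 1 − 0.70 × 0.80 = 0.44, 1 − 0.85 × 0.80 = 0.32, and 0.32/0.44 = 0.73. The index-only share is 0.70 × 0.20/0.44 = 0.32. Power uses the two-proportion normal approximation with pooled variance under the null and two-sided alpha 0.05.

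With p = 25% and 15% (risk ratio 0.60), the same q values of 10%, 20% and 30% give 0.72, 0.80 and 0.85.

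Table 1 lists counts. If the mean numbers of new events are 0.30 and 0.15, index events add to both means. With 0.20 added, the ratio is 0.35/0.50 = 0.70 instead of 0.50. The difference in means stays at 0.15, but with more noise around it.

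**ITT coding of unreleased participants.** With 5% unreleased in each arm, 0.30 × 0.95 = 28.5% and 0.15 × 0.95 = 14.25%. The risk ratio stays at 0.50, and power is 0.693 against 0.700 for released participants only. With no true effect and unequal non-release of 2% and 8%, the ratio is 0.98/0.92 = 1.07. With 5% and 15% it is 0.95/0.85 = 1.12.

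**The case against.** The strongest reply is that the article is silent on attribution and does not say that index-case outcomes count. Recidivism ordinarily means new offending, charge types are collected and could support a split, and a full protocol or SAP may hold the linkage rule. Part of this stands: a reader might infer that the plan deliberately counts every post-release conviction, and the text does not go that far. But the article does more than leave a detail out. It gives an explicit definition whose conviction and incarceration components do not fit a wholly pre-trial cohort, and a later document would have to narrow that wording.

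A reader might also infer that a fixed share of the treatment effect, such as half, would be lost. The documents do not support this. No pooled any-event endpoint is stated, Table 1 lists separate measures, and models are to follow the nature of each outcome. An index-case conviction does not enter the arraignment count. Nor do the documents show how many index cases remain open at release, or that convictions would mostly be index-case convictions.

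Finally, it is tempting to say that the ITT rule causes the mixing or makes continued custody a success in the main result. It does neither. It concerns people who were never released, sits in a secondary analysis and covers an expected share below 5%. It leaves the ratio unchanged when non-release is equal by arm. The article already plans a Fisher's exact test of release by arm.

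**Conclusion.** The point holds as a defect of definition. As written, the 90-day conviction and incarceration measures can include dispositions of the index case for participants released with that case pending. The effect would be inflated absolute rates in both arms and a ratio drawn towards 1. If index-case events are equally frequent in the two arms, this dilutes a difference and does not create one. The size cannot be determined from the article. The ratios above rest on assumed rates, on equal index-case rates by arm and on independence. The consequence is limited to a tertiary outcome.

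Two minor points stand beside it. Planned analyses speaks of rearrests, which is not among the components defined under Secondary and tertiary outcome measures. The ITT coding gives an event-free value to people whom the same section describes as not at risk.

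**What to change.** - Count arraignments, incarcerations and convictions as recidivism only when they are tied to an offence dated after release, using the CJIS charge and case data.
- Report convictions and incarcerations on the index case separately, by arm, as index-case dispositions.
- Use one event term in the outcome definition and in Planned analyses. Either replace rearrest with a defined component such as arraignment, or add rearrest to the definition.
- State that the released-only (mITT) analysis is the main one for recidivism. Label the ITT analysis that codes unreleased participants as not rearrested as a sensitivity analysis, since they are not at risk.

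The cost is a change of wording and somewhat more record linkage. It assumes that the CJIS extracts carry offence or case dates, which the article does not say and which should be confirmed before data are requested. Fewer events will be counted, and new-offence convictions within 90 days may be few. That is a limit of the window, which index-case events would otherwise hide.

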### Study procedures

#### Administrative approvals

The NYU Langone Health Institutional Review Board (IRB), which serves as the single IRB, reviewed and approved the study with the Middlesex County Sheriff’s Office and the Tufts University School of Medicine. To further protect the privacy of study participants, the National Institutes of Health (NIH) issued a Certificate of Confidentiality. In addition, given that this study includes prisoner involvement, approval was received from the Office of Human Research Protections (OHRP). The study has been registered on clinicaltrials.gov (NCT05481112).

The trial will be carried out in accordance with International Conference on Harmonization Good Clinical Practice (ICH GCP) and the following: (1) United States (US) Code of Federal Regulations (CFR) applicable to clinical studies (45 CFR Part 46, 21 CFR Part 50, 21 CFR Part 56, 21 CFR Part 312, and/or 21 CFR Part 812), (2) All key personnel and clinical trial site staff who are responsible for the conduct, management, or oversight of this trial will complete Human Subjects Protection and ICH GCP Training.

#### Screening

Research staff will review jail records to identify potentially eligible participants. Thereafter, they will arrange to meet individuals in person to share preliminary information about the study and, if interested, complete the in-person screening process. This process will include asking if they are willing to accept randomization to the experimental or enhanced usual care condition and ensuring that they are able to provide written informed consent in English. Eligible and interested participants will be invited to begin the consent process.

#### The consent process

Consent forms will describe, in detail, the study intervention, study procedures, and risks. Informed consent is required prior to starting the study intervention. Participants will be provided with a copy of the informed consent form. Trained research staff will review the consent form making sure to explain the study including a review of the study purpose, procedures, potential risks and of the rights of research participants. Participants will be informed that participation is voluntary and that they may withdraw from the study at any time, without prejudice, nor impacts on their ongoing services received. They will also be notified that a Federal Certificate of Confidentiality has been obtained to encompass protocol activity and further protect confidential study participation. Staff will answer any questions that may arise.

This conversation will take place in a private room or private area on the unit. Participants will have the opportunity to carefully review the written consent form and ask questions prior to signing. The participant will be offered the opportunity to discuss the study with anyone they so choose or take time to think about their choice prior to agreeing to participate. If they choose to participate, the participant will sign the informed consent document. A copy of the informed consent document will be given to the participants for their records.

#### Random assignment

Randomization of eligible participants will occur within one week after screening. A randomization module has been created on REDCap, using a 1:1 permuted block design. Study assignment is unblinded. Participants and medical staff will be notified of the study arm assignment. It is anticipated that screening, the consent process, randomization, and treatment induction will likely occur within a 5-day window. While randomization to the experimental condition will not guarantee XRB induction, every practical effort will be made to induct participants onto XRB prior to release. It is, however, the nature of the unsentenced population that release dates are unpredictable. The percentage of participants in the experimental condition who do initiate XRB prior to release will be an important implementation finding of this project.

##### SLB

As described above, participants will already be receiving SLB and be participating in the MATADOR program. If randomized to the SLB arm, they will continue treatment as usual in the facility.

##### XRB

The Sublocade packaging states that patients with OUD who are not on an active SLB dose may receive XRB if they are able to tolerate a 4 mg dose. If this dose is tolerated for an hour without precipitated withdrawal, the initial monthly injection can be administrated. As previously mentioned, XRB injections start at 300 mg for the first 2 months, usually followed by monthly maintenance doses of 100 mg. Study clinical staff will have flexibility to continue the 300 mg dose for greater than two months, or use the 100 mg dose for initial induction, based on FDA-labeling for XRB dosing, if the participant’s opioid use history or clinical status at the time of dosing support these decisions. Medication induction and maintenance will be conducted in accordance with the FDA-approved labeling and associated guidelines.

Jail medical staff will be encouraged to deliver XRB in a manner consistent with the FDA label and this protocol, but also in a flexible, pragmatic paradigm given staffing, internal policies, clinical settings, additional counseling resources, and general medical and psychiatric care at MJHOC, which may impact and interact with study treatment. (Based on the study physician’s experience, most XRB participants are expected to remain on the higher dose.) This protocol explicitly welcomes and tolerates these types of real-world factors, and potential confounders, consistent with an open label effectiveness trial or pragmatic trial. Medication treatment is free-of-charge but not otherwise incentivized.

##### Dosing timelines and release

In both SLB and XRB conditions, patients will be encouraged to continue their treatment outside of the facility. Both forms of treatment that are offered in the study are available to participants in the community. Designated MATADOR staff at the MJHOC create appointments for patients to continue receiving their medication in the community. These appointments are set up prior to release, however it is the patients’ responsibility to follow through with these appointments and continue their treatment. Patients are also given a bridge script for their medication prior to discharge in attempt to avoid lapses in treatment.

##### XRB injection procedures

###### XRB induction

Patients randomized to the XRB condition will first receive a 4 mg dose of sublingual buprenorphine followed by the XRB injection an hour later, if there is no precipitated withdrawal, based on package insert recommendations. XRB will be delivered as a pre-filled 2 cc subcutaneous monthly injection, using a 300 mg starting dose in most cases. Study staff may elect to use the 100 mg dose for initial injection, if over-sedation is deemed to be a higher-than-average risk (for instance, if the participant experienced over-sedation during the SLB up-dosing). XRB consists of a depot injectable formulation in polymeric solution to the abdomen and releases buprenorphine over 28-days (4-weeks) by diffusion as the polymer biodegrades.

###### XRB maintenance

Participants will receive XRB monthly from the time of induction to the day of release, sentencing, or transfer. Study clinicians will generally adhere to FDA-labeling on XRB dosing, which recommends two months of 300 mg doses followed by maintenance doses of 100 mg monthly for the remaining four months. The maintenance dose may be increased to 300 mg monthly for patients who tolerate the 100 mg dose, but do not demonstrate a satisfactory clinical response, as evidenced by self-reported illicit opioid use or urine drug screens positive for illicit opioid use. Indivior data indicates that 300 mg continuous dosing may be more effective for people experiencing fentanyl-involved OUD. XRB can be administered subcutaneously in the abdomen, thigh, buttock, or back of the upper arm at each 28-day visit with a minimum of 26 days between doses. In the event of a missed visit, the dose can be delivered within 28 days (up to 8 weeks since the prior dose). Longer missed dose windows will require another brief SLB lead-in prior to the next injection.

#### Study medication storage

Each single XRB dose is packaged in a carton in a prefilled syringe with safety needle. It is stored in refrigerator at 2–8 °C (35.6–46.4 °F). Once outside the refrigerator this product may be stored in its original packaging at room temperature, 15–30 °C (59–86 °F), for up to seven days prior to administration. The product requires at least 15 min to reach room temperature.

